### ***Secondary & Tertiary Outcomes***

Analyses will be descriptive; no alpha has been allocated. Point and interval estimates for the effect of the intervention on each of the secondary outcomes at six and 12 months will be determined separately using linear mixed models. Multiple linear regression analyses will also be performed to explore the association between change in cognitive function, after accounting for experimental group, baseline age, baseline global cognition, and: 1) superior treatment adherence; 2) change in physical activity levels outside the research protocol; and 3) change in general balance and mobility. Randomization integrity will be determined by examining bias in the blocking sequence used to produce allocation sequence.

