### ***Proof-of Concept Outcome Measures***

Feasibility outcomes for delivering the intervention (i.e., adherence) will be measured throughout the 6-month intervention period. Class attendance will be recorded by the instructors.

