### **Interventions**

All exercise-based classes will be led by instructors who have formal expertise in delivering group exercise programs to older adults. All classes will be 60 minutes in duration. All classes will have a maximum participant to instructor ratio of 4:1. Class attendance will be recorded by the instructors. To minimize contamination, only one class will occur at any given time in the same facility. In addition, there will be a minimum of 30 minutes between classes at any given facility. All intervention groups will include twice-weekly classes of 60 minutes each over 26 weeks. Fidelity across instructors and across time will be ensured by providing instructors with detailed protocols including pictures; regular observation and intervention classes by study PI and coordinator and auditing with standard checklist to ensure intervention content is delivered accurately and consistently; and videotaping classes from each intervention arm across time.

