### ***CON Group***

The CON program will follow the protocol used in [name] previous RCT. The CON protocol will consist of stretches, deep breathing and relaxation techniques, general posture education, general core control exercises, grip strength and dexterity exercises, and light

isometric toning exercises. Some exercises from the EX program will also be included but in a simplified format without progression (e.g., double calf raises, heel and toe tapping, balance exercises). Once a month, the class will consist of educational lecture and will include topics such as sleep hygiene, goal setting, and nutrition. This group will serve to control for confounding variables such as physical training received by traveling to the community centre for twice-weekly classes and changes in lifestyle secondary to study participation. The Timed-Up-and-Go task will be completed on a monthly basis to allow for objective physical performance tracking.

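### The planned adherence regression gives one attendance slope over all three arms, control included, so it cannot be attributed to either intervention; arm-specific slopes should be reported beside it.

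*Protocol*

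**What the plan says.** In the protocol's Secondary & Tertiary Outcomes section, the model for adherence is set out as an association to be explored "after accounting for experimental group, baseline age, baseline global cognition, and: 1) superior treatment adherence". The outcome is change in cognitive function and the method is multiple linear regression. Two further regressors follow, change in outside physical activity and change in balance and mobility. The section states no group-by-adherence term, no fit by arm and no restriction to EX and Cog-Plus. It gives the status of these analyses as "Analyses will be descriptive; no alpha has been allocated".

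Adherence is class attendance. Under Proof-of Concept Outcome Measures, "Feasibility outcomes for delivering the intervention (i.e., adherence) will be measured throughout the 6-month intervention period", and instructors record attendance. It exists on the same scale in every arm: "All intervention groups will include twice-weekly classes of 60 minutes each over 26 weeks".

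The CON Group section gives the control classes a comparator role: "This group will serve to control for confounding variables such as physical training received by traveling to the community centre for twice-weekly classes". Their content is stretching, relaxation, posture and core work and light toning, together with some EX exercises in simpler form that are not progressed. In addition, "Once a month, the class will consist of educational lecture".

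**The concern.** With group entered as a main effect only, group shifts the intercept and attendance has one slope for everyone. That slope averages over three different things: attending progressive exercise, attending cognitive and social activity, and attending the control classes. The regressor is called treatment adherence, yet attendance at the comparator counts towards it in the same way as attendance at an intervention.

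Two consequences follow. An association present only in the active arms is diluted by CON. Conversely, if people who attend well tend to improve more in any arm, the pooled slope picks that up and nothing in the model sets it apart. The Introduction faults an earlier multi-component trial because its effects could not be assigned to one component, and says this trial is meant to inform a larger one. A slope that cannot be assigned to an arm helps little with either purpose.

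**Working it through.** The protocol states no figure for this regression, so there is none to reproduce. The check asks what the stated model estimates.

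**Inputs**
- Arm sizes 34, 34 and 52, total 120 (Sample Size Calculation). That section uses other labels for two arms; I match them to Cog-Plus and CON through the 2:2:3 ratio in Treatment Allocation and Concealment.
- 15% attrition (same section): 34 × 0.85 = 28.9 and 52 × 0.85 = 44.2, so about 29/29/44 completers.
- Scheduled classes: 2 × 26 = 52 in every arm.
- Assumed, not in the protocol: equal within-arm attendance variance, equal residual variance and continuous attendance.

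**Weights.** In a regression with group main effects and one attendance term, the common slope is

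b_pooled = Σ n_k s_k² b_k / Σ n_k s_k²,

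where s_k² is the attendance variance within arm k. With equal s_k² the weights are n_k/120:
- EX 34/120 = 0.283
- Cog-Plus 34/120 = 0.283
- CON 52/120 = 0.433

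With completers, the CON weight is 44/102 = 0.431.

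**Dilution**
- Slope b in both active arms, 0 in CON: 68/120 × b = 0.57b.
- Slope b in EX only: 34/120 × b = 0.28b.
- The same association a in every arm: the pooled slope is a, and EX minus CON is 0.

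**Sensitivity to the variance assumption.** With 29/29/44 and CON attendance variance r times that of the other arms, the CON weight is 44r/(58 + 44r). For r = 0.25 it is 11/69 = 16%. For r = 4 it is 176/234 = 75%.

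**Simulation.** 4,000 runs with 29/29/44 completers, attendance SD 1 and residual SD 1. Slopes are in SD of change per SD of attendance, and all slopes are assumed:

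| True slopes EX / Cog-Plus / CON | Mean pooled slope | Mean EX minus CON slope |
|---|---|---|
| 0.5 / 0.5 / 0 | 0.28 (SE 0.11) | 0.51 (SE 0.25) |
| 0.5 / 0 / 0 | 0.14 | 0.51 |
| 0.3 / 0.3 / 0.3 | 0.30 | 0.00 |

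The first and third rows are opposite situations, yet the pooled slope is nearly the same in both. The arm-specific difference tells them apart.

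**Precision.** With equal variances, SE(b_k) is proportional to 1/√n_k. Relative to the pooled slope:
- both active arms combined minus CON: √(1/68 + 1/52) / √(1/120) = 2.02
- one active arm minus CON: √(1/34 + 1/52) / √(1/120) = 2.42

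**The case against.** The strongest reply is that the protocol promises little here. It explores an association, descriptively and without alpha, and never speaks of dose or dose-response. For that purpose a group-adjusted common coefficient is a legitimate summary, and adjusting for group does remove between-arm differences in mean attendance. This stands, and it keeps the severity low. A descriptive slope should still describe something identifiable, and this one mixes three activities.

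Second, the common slope is inferred from the covariate list, and a statistical analysis plan could add interactions or fits by arm. That is fair. But the protocol names the adjusters itself, and as named they yield a common slope, so an analysis plan with arm-specific slopes would be changing this text. Adherence is also undefined as continuous or as a threshold. With a threshold, the same weighting applies with s_k² = p_k(1 − p_k), where p_k is the share of good attenders in arm k, and the exact figures change.

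Third, a reader might infer that the analysis cannot show any effect of attendance. The figures do not support that. An effect is diluted, not lost: in the 0.5/0.5/0 simulation the pooled slope crosses a two-sided 5% threshold in 76.5% of runs, against 54% for EX minus CON. With slope b in both active arms, and in units of the pooled standard error, the pooled slope gives 0.57b, the combined active-minus-CON contrast b/2.02 = 0.50b and a single-arm contrast b/2.42 = 0.41b. What is lost is attribution.

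Fourth, a reader might infer that the active-minus-CON difference should replace the pooled slope as the true dose-response estimate. The documents do not support that either. CON contains some simplified EX exercises, so it is an imperfect negative control. The tendency of good attenders to do better may differ between progressive exercise and unprogressed stretching. Attendance arises after randomisation, so slope differences are not randomised comparisons. These limits stand and must accompany the arm-specific results.

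**Conclusion.** The point holds as a modest one. As the protocol reads, the adherence regression gives one attendance slope over all three arms. That slope cannot be attributed to EX or Cog-Plus, or separated from a general association between attending well and improving.

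Under equal attendance variance, CON carries 43% of the weight and an active-arm slope shrinks to 0.57b, or to 0.28b if only EX has it. These values rest on a variance assumption that the protocol does not inform: the CON weight runs from 16% to 75% as its relative variance goes from 0.25 to 4. The lack of attribution does not depend on that assumption.

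The primary Dunnett contrasts, the sample size and the feasibility criteria do not use this coefficient. Severity is low.

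**What to change.** In the Secondary & Tertiary Outcomes section:

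1. Define adherence as the proportion of scheduled classes attended, kept continuous.
2. Add a group-by-adherence term to the adherence regression.
3. Report the slope with its interval in each arm, and the EX-minus-CON and Cog-Plus-minus-CON slope differences, alongside the pooled slope.
4. Label all of these descriptive and non-randomised, and note that CON is an imperfect negative control because of its overlap with EX.

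This needs two interaction coefficients for three arms and no new data. The arm-specific results are less precise, by the factors of about 2.0 to 2.4 shown above, so the intervals will be wide and should be presented as such. Keeping the pooled slope in the report preserves the more precise summary.

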### ***Economic Evaluation – A Cost-utility analysis***

Our economic evaluation will examine the incremental costs and effects generated by using a 1) 6-month targeted exercise training program or a 2) 6-month cognitive and social enrichment program among older adults with chronic stroke compared with a 6-month stretch and tone program (i.e., control; comparator). The outcome of our cost effectiveness analysis is the incremental cost-utility ratio (ICUR). By definition, an ICUR is the difference between the mean costs of providing the competing intervention divided by the incremental difference in QALYs, where  $ICUR = \Delta \text{Cost} / \Delta \text{QALY}$ . QALYs are calculated based on the quality of life of a patient (measured using health state utility values estimated from the EQ-5D-3L) in a given health state and the time spent in that health state. For any missing data, we will use a combination of imputation and bootstrapping to quantify uncertainty due to missing values.

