An alternative or supplemental behavioral approach might be to intervene with cognitive and social enrichment activities to ameliorate cognitive impairment in the chronic stroke phase. The premise of this strategy is that by engaging in activities that stimulate higher-order cognition (e.g., memory and executive function), cognitive performance is improved and future cognitive decline is mitigated. Rodent models suggest that environment enrichment—e.g., housing in larger cages and in larger groups with varied environmental features—has various positive behavioural, neuro-anatomical, and molecular effects, including following stroke. Few previous studies have tested this proposition among humans with chronic stroke. One 6-month pre-post study showed that a program that combined exercise training using the FAME program (2 days/week) with cognitive and social enrichment (1 day/week) was associated with benefits in aspects of memory and executive functions among individuals who had sustained a stroke at least 12 months prior. Another pilot RCT compared this same multi-component intervention to a wait-list control and found benefits to aspects of executive functions, working memory, and physical functioning. Whether these effects could be attributed primarily to the exercise training or to the social and cognitive activities could not be determined by this study design.

Thus, to better understand the relative effects of exercise training and of cognitive and social enrichment on cognitive function, we aim to conduct a 3-arm, parallel group proof-of-concept RCT comparing the following: 1) exercise training; 2) cognitive and social enrichment activities; and 3) an active control group consisting of stretching and toning activities. Each intervention arm will be 6 months in length and will be followed by a 6-month follow-up period. The results of this proof-of-concept RCT will be used to inform the design of a larger definitive trial. Specifically, it will confirm the feasibility of the study methods and procedures.

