### ***Cog-Plus Group***

We have designed this program based on the feedback received from our pilot study and based on current evidence. In addition, we aimed to design a program that could feasibly be implemented in the community with minimal resources. Because impairment in multiple cognitive domains is common following stroke, the cognitive exercises included in the program targeted various aspects of cognition, including learning and memory, processing speed, attention, working memory, and executive functions. Each class will begin with the participants being asked to memorize a 7-item word list. Next, each participant will complete approximately 15 minutes of the brain training program Lumosity using an individually-issued Apple iPad. Lumosity consists of various short games (typically 1 to 5 minutes) that target various aspects of cognition (e.g., working memory, divided attention, processing speed). Each class, participants will be encouraged to complete at least 5 distinct games. For the remaining class time (approximately 30 minutes), the participants will complete a variety of social games and mental activities in pairs or as entire class. Some of these activities will utilize apps on the Apple iPads (e.g., *Heads-Up*, *Teledoodle*), and others are based on improvisation and mental activities from the PERK program^64. At the end of class, participants will recall as many of the words from the word list; they will use the Notes program on the iPad to record the recalled words. Approximately every month, the class instructor will meet individually with the participants to show performance progress on the Lumosity training program and to discuss outstanding concerns and areas of improvement (e.g., short-term memory, speed of responding). Every month, the 7-item word list will be replaced with a 15-item word list, and participants will be requested to recall those words immediately, as well as at the end of the class.

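### The cost-utility analysis compares each active programme only with control, so the planned ICURs do not report the increment between EX and Cog-Plus, and a programme that is poor value next to the other can look favourable.

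*Protocol*

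**What the plan says.** The relevant text is the Protocol section Economic Evaluation – A Cost-utility analysis. It will evaluate a "6-month targeted exercise training program or a 2) 6-month cognitive and social enrichment program", each "compared with a 6-month stretch and tone program (i.e., control; comparator". The result to be reported is named: "The outcome of our cost effectiveness analysis is the incremental cost-utility ratio (ICUR"). The ratio is defined as "the difference between the mean costs of providing the competing intervention divided by the incremental difference in QALYs".

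The section gives no EX versus Cog-Plus ratio, ordering of the three options, dominance check or net-benefit comparison. It also gives no willingness-to-pay threshold and no rule for calling a programme cost-effective. Bootstrapping is mentioned only in connection with missing values. No other section of the protocol supplies the missing comparison.

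Three other places bear on the point:
- The Introduction describes a "3-arm, parallel group proof-of-concept RCT comparing the following" exercise, enrichment and control. Its stated purpose is "to better understand the relative effects of exercise training and of cognitive and social enrichment on cognitive function".
- The Introduction also says: "An alternative or supplemental behavioral approach might be to intervene with cognitive and social enrichment activities". So the programmes are not presented as strictly exclusive in practice, although no combined arm is tested.
- Of Cog-Plus, the section Cog-Plus Group says "we aimed to design a program that could feasibly be implemented in the community with minimal resources". This is a design aim and gives no cost, but it shows that relative resource use matters to the sponsor.

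**The concern.** When three options are on the table, a ratio against one common baseline answers whether each option is worth having instead of the baseline. It does not answer which option to choose. For that, the options are ordered by cost. Those that cost more and give less are identified (dominated), as are those bettered by a mix of two others (extendedly dominated). Each remaining option is then compared with the next cheaper one.

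Here the baseline is a stretch and tone programme that the section CON Group describes mainly as a control for confounding influences. The practical question after the trial is likely to include which active programme to take forward, and the planned economic outcome leaves that step out. A reader shown two ratios, both acceptable, could take both programmes to be good value when the extra money for the dearer one buys little or nothing beyond the other.

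The gap is separate from the efficacy contrasts. An added EX versus Cog-Plus contrast on the ADAS-Cog-Plus would not fill it.

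**Working it through.** **Inputs.** The protocol gives no cost, QALY, ICUR or threshold, so it has no economic figure to reproduce. All costs, QALYs and thresholds below are assumptions chosen to show what can happen. From the protocol come the definition ICUR = Δcost / ΔQALY and the arm sizes in Sample Size Calculation (34 and 34 in the active arms, 52 in control). Net monetary benefit against control is NMB = threshold × ΔQALY − Δcost.

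**Step 1. A case in which both look acceptable against control.** Assumed mean cost and QALYs:

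| Arm | Cost | QALY | Δcost vs CON | ΔQALY vs CON | ICUR vs CON |
|---|---|---|---|---|---|
| CON | 1,000 | 0.300 | – | – | – |
| Cog-Plus | 1,100 | 0.305 | 100 | 0.005 | 100/0.005 = 20,000 |
| EX | 1,500 | 0.311 | 500 | 0.011 | 500/0.011 = 45,455 |

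EX against the next cheaper option, Cog-Plus: (500 − 100)/(0.011 − 0.005) = 400/0.006 = 66,667 per QALY.

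At an assumed threshold of 50,000:
- NMB for Cog-Plus = 50,000 × 0.005 − 100 = 150.
- NMB for EX = 50,000 × 0.011 − 500 = 50.

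Both are positive against control, but Cog-Plus is the better choice. Above a threshold of 66,667 the choice switches to EX.

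**Step 2. A dominated programme can also look acceptable.** Assumed increments against CON: EX +400 and +0.03 QALY (400/0.03 = 13,333); Cog-Plus +800 and +0.02 QALY (800/0.02 = 40,000). Cog-Plus costs 400 more than EX and gives 0.01 QALY less, so it is dominated. Its ratio against control is still below 50,000. NMB at 50,000 is 50,000 × 0.03 − 400 = 1,100 for EX and 50,000 × 0.02 − 800 = 200 for Cog-Plus.

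**Step 3. The problem need not arise.** Assumed increments: EX +400 and +0.02 (20,000); Cog-Plus +500 and +0.03 (500/0.03 = 16,667). Cog-Plus against EX is 100/0.01 = 10,000. NMB at 50,000 is 50,000 × 0.02 − 400 = 600 for EX and 50,000 × 0.03 − 500 = 1,000 for Cog-Plus. The programme with the lower ratio against control is also the best choice, so the control-only ratios do not mislead about Cog-Plus.

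**Step 4. The two ratios alone do not determine the third.** Keep EX at +500 and +0.011 as in step 1, and set Cog-Plus at +400 and +0.02. The ratios against control are again 45,455 and 20,000. Now EX costs 500 − 400 = 100 more than Cog-Plus and gives 0.02 − 0.011 = 0.009 QALY less, so it is dominated. The same pair of ratios is compatible with 66,667 per QALY and with dominance. The increments themselves are needed.

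**Step 5. Precision.** Assume a QALY SD of 0.05 to 0.10 and no attrition.
- EX minus Cog-Plus: SE = SD × √(1/34 + 1/34) = SD × 0.2425, or 0.012 to 0.024. That is two to four times the 0.006 QALY difference in step 1.
- Either active arm minus CON: SE = SD × √(1/34 + 1/52) = SD × 0.2206, or 0.011 to 0.022.

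The missing increment is imprecise, but only slightly more so than the comparisons already planned.

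**The case against.** Several arguments on the other side have force.

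- **No decision rule.** A reader might infer that the plan will declare a poor programme cost-effective or select the wrong one. The protocol does not support that. It sets no threshold and has no selection step, so the harm is a possible misreading of the reported ratios. This stands.
- **Dominance can be recovered.** A reader might also infer that dominance between the active programmes could never be seen. That goes too far. Both sets of increments are taken from the same control arm, and the section undertakes to examine incremental costs and effects. If these are reported, the EX versus Cog-Plus point estimate follows by subtraction, as in step 1. What stands is narrower: the named outcome is the ratio, two ratios are not enough (step 4), and the uncertainty of the third comparison needs a joint analysis because both planned comparisons share control.
- **The programmes may be combinable.** The Introduction allows enrichment to supplement exercise. If the two could be given together with roughly additive effects, ratios against a common comparator would be defensible. This limits the point to the programmes considered as alternatives. That is how the economic section frames them, with an either-or wording and a reference to competing interventions, and no combination is tested.
- **The comparator matches the efficacy contrasts.** The two Dunnett contrasts are also against control, and value against control is a coherent question. It is a reason to keep those ratios, but it does not make them sufficient for a choice among three options.
- **Detail may sit in an SAP.** None is at hand, and it could add these steps. The protocol does, however, fix the comparator, and that statement is incomplete for three options.
- **Imprecision.** With 34 per active arm, a reversal as small as in step 1 would be uninformative. This stands as a reason to call the result exploratory, but it applies almost equally to the planned ratios (step 5).

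**Conclusion.** The point holds in a limited form. The planned economic outcome omits the increment between the two active programmes. When they are viewed as alternatives, a programme that is dominated by the other, or poor value next to it, can look favourable against control.

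The size cannot be derived from the protocol. The figures of 20,000, 45,455 and 66,667 per QALY rest wholly on assumed costs and QALYs, and the contrast at 50,000 rests on an assumed threshold. They show that a reversal is possible, and step 3 shows that it is not inevitable.

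The comparisons with control are not wrong and need not be removed. This is a secondary analysis in a proof-of-concept trial, and neither the primary inference nor data collection is affected. The change is worth making because the results are meant to inform a larger trial and the remedy is cheap.

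**What to change.** In Economic Evaluation – A Cost-utility analysis, keep the two ICURs against CON and add:

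1. Mean costs and QALYs for all three arms, and a fully incremental comparison: order the arms by mean cost, identify dominated and extendedly dominated options, and report each remaining option's ICUR against the next cheaper non-dominated one. Net monetary benefit across the three arms is an equivalent alternative.
2. One sentence stating that sampling uncertainty will come from a joint bootstrap of all three arms, giving the probability that each is optimal over a range of thresholds. The present text ties bootstrapping only to missing values.
3. A statement that this comparison treats the programmes as alternatives, as tested, and that the EX versus Cog-Plus increment is exploratory because it will be imprecise with about 34 participants per active arm.

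The cost is a few sentences and a few lines of analysis code. No new data, participants or procedures are needed.
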